## Conceptual Framework

Based on the findings of the above literature, the following conceptual framework is developed (Figure 1). The conceptual framework shows that the different risk factors cause POP either through direct damage of pelvic muscles (levator-ani muscle and its nerve supply) or by causing collagen to weaken ([37](#_ENREF_37), [39](#_ENREF_39), [47](#_ENREF_47), [50](#_ENREF_50), [56](#_ENREF_56), [57](#_ENREF_57), [61](#_ENREF_61), [65](#_ENREF_65), [68](#_ENREF_68), [76](#_ENREF_76), [78](#_ENREF_78), [81](#_ENREF_81), [86](#_ENREF_86), [87](#_ENREF_87)).

**OBESTETRICS/GYNECOLOGY**

- Vaginal delivery
- Parity
- Instrumental delivery
- Age at 1^st^ delivery
- Prolonged labour
- Menopause
- History of pelvic surgery/hysterectomy

**SOCIO-DEMOGRAPY**

- Age
- Level of education
- Occupation (weight lift)
- Ethnicity/race

**MEDICAL CASES**

- Chronic cough
- Constipation
- DM

DM

**Family History of Pelvic Organ Prolapse**

**Pelvic Organ Prolapse (POP)**

**Nutritional factors**

- BMI > 24Kg/m^2^
- BMI < 18 Kg/m^2^

**Pelvic Organ Prolapse symptoms**

**Pelvic Floor Muscle Training**

**Prolapse-QoL**

Figure 1: Conceptual framework indicating risk factors and impacts of Pelvic Organ Prolapse. Compiled from related literature, 2022.

## Impact of POP on Health-Related Quality of Life

POP is a complicated disorder with both physical and functional elements ([88](#_ENREF_88)), and as a result, it can have a substantial influence on the quality of life and psychological well-being of women who are affected. Indeed, prolapse can cause a number of urinary, bowel, and sexual disorders, all of which can negatively impact a patient's quality of life. Sexual dysfunctions, in particular, are quite frequent in women with POP ([32](#_ENREF_32), [88](#_ENREF_88), [89](#_ENREF_89)). POP patients usually complain problems with sexual desire, arousal, orgasm, and pain, which can lower their quality of life and negatively impact their relationships ([32](#_ENREF_32)). Social, physical, and psychological constraints caused by pelvic organ prolapse may have an impact on a patient's interpersonal connections also ([90](#_ENREF_90), [91](#_ENREF_91)). A study conducted among 3,114 middle aged women (50 -61) reported that, the presence of POP symptoms was linked to a lower quality of life score on each domain of health (physical mobility, pain, emotional reaction, social isolation, energy, and sleep ([92](#_ENREF_92)). Other similar studies also reported that POP causes physical, social, psychological, occupational, household, and/or sexual limits in women, producing severe symptomatic distress and poor quality of life ([90](#_ENREF_90), [92](#_ENREF_92)). Moreover, it is recommended that the major goal of treatment should be to improve health-related quality of life by reducing this symptoms. For the clinical assessment to develop more appropriate treatment, the severity and impact of prolapse symptoms on quality of life are critical ([93](#_ENREF_93)).

## Interventions against POP

The risk factors that have been identified to be predisposing factors are both non-modifiable (family history, ethnicity, and age) and modifiable (obesity, underweight, heavy lifting, and chronic medical problems). Lifestyle modification is recommended to reduce the risk of POP caused by modifiable risks ([1](#_ENREF_1), [3](#_ENREF_3), [17-19](#_ENREF_17)). Once the POP is developed it is managed either by conservative management or by surgical management.

### Conservative Management

Recent evidence and guidelines recommend conservative management for mild degree prolapse with no symptoms ([1](#_ENREF_1), [42](#_ENREF_42), [94](#_ENREF_94)). Non-surgical therapy such as pessary, pelvic floor muscle training, or both can help with symptom relief as well as weight loss in obese people. However, for women with severe prolapse, most of these treatments are ineffective; hence, surgical therapy is more appropriate rcumstances ([95](#_ENREF_95), [96](#_ENREF_96)).

1. **Pessary**: is a device inserted into the vagina to support the descending vaginal compartment ([3](#_ENREF_3), [94](#_ENREF_94)). While it is effective in managing mild degree prolapse, there are risks of infection and irritation ([9](#_ENREF_9), [19](#_ENREF_19), [97](#_ENREF_97)). Moreover, the use of pessary is not well implemented in low-income countries including Ethiopia (except the one under pilot study).
2. **Pelvic Muscle Training**: The importance of Pelvic Floor Muscle Training to relieve POP symptoms and its effectiveness was frequently confirmed by Randomized Control Trials from developed countries. However, still, evidence from low-income countries is lacking on its feasibility and effectiveness. In this document, the findings from previous literature are discussed in detail, as it is part of the current and planned study.

Trial studies were conducted in westerns to evaluate the effect of pelvic floor muscle exercise on the reduction of prolapse symptoms, improving prolapse stage, and prevention of secondary prolapse. A review of six trail papers published between 1996-2010 shows that pelvic floor muscle exercises improved prolapse symptoms by 17% compared to the control groups ([94](#_ENREF_94)). A randomized control trial conducted on women aged 55 years and over with mild symptoms shows that 57% of women in the pelvic floor muscle training (PFMT) group have improved symptoms after 3months of training while improvement was seen only in 13% of control groups ([44](#_ENREF_44)).

Another systematic review of 13 papers which included 2,340 patients also shows that women in the Pelvic Floor Muscle Training get improvement than the control groups in prolapse symptom score with a mean difference of -3.07 ([98](#_ENREF_98)).

A study conducted among 109 Scandinavian-speaking women with POP stage I –III show that 39% of women who received lifestyle advice and Pelvic Floor Muscle Training reported improved sexual function compared to only 5% of women who received lifestyle advice only ([99](#_ENREF_99)). Similarly, a multicentre randomized control trial conducted in 23 centers in the United Kingdom, New Zealand, and Australia show that after 16 weeks of individualized pelvic muscle training, 12 months of prolapse symptoms were significantly less in interventional groups ([42](#_ENREF_42)).

There are contradicting findings on regarding the effect of PFMT on improving the prolapse stage. A randomized control trial study in Norway involving 109 women shows that Pelvic Floor Muscle Training improved at least one pelvic organ prolapse quantification system stage in 19% of participants ([100](#_ENREF_100)). However, other controlled trial studies reported that there was no change in the prolapsed stage ([42](#_ENREF_42), [101](#_ENREF_101)). Other studies reported that the effect of physical exercise on pelvic muscle strength is controversial and needs an adequate sample size for generalization ([101](#_ENREF_101), [102](#_ENREF_102)). A recent (2021), Systematic review and meta-analysis of randomized control trial studies concluded that even though PFMT significantly changed the self-reported symptom as improved, there was no distinct difference on POP-SS ([103](#_ENREF_103)).

To evaluate the effect of various treatments to treating POP, the most significant outcome is quality of life. It is suggested that researchers explain how POP treatment affects quality of life. A vast number of researches have investigated the impact of various treatments by assessing quality of life ([94](#_ENREF_94), [104](#_ENREF_104)). Randomized control trial studies show that PFMT has significantly improved prolapse-quality of life. An assessor blinded pilot study conducted on 29 POP patients for 16 weeks showed that POP-related symptoms such as stress urine incontinence, frequency, post micturition dribbling, and bowel obstruction decreased dramatically. As a result, the overall health, physical limits, emotion, and severity assessments all had considerably improved after PFMT ([105](#_ENREF_105)). Similarly, a systematic review and meta-analysis study conducted to evaluate quality of life after POP treatments showed that PFMT had a relative influence on quality of life ([106](#_ENREF_106)). Another two randomized control trial studies also showed that PFMT significantly improved bowel-related quality of life ([107](#_ENREF_107), [108](#_ENREF_108)).

While these all findings are from developed countries, there is a lack of evidence from low-income countries including Ethiopia.

### Surgical management of POP

In developing countries, women seek treatment at an advanced stage of prolapse and are usually managed surgically ([26](#_ENREF_26), [35](#_ENREF_35), [56](#_ENREF_56), [61](#_ENREF_61), [73](#_ENREF_73)). Surgical management is mainly classified as reconstructive and obliterative. Obliterative surgery is usually performed for elderly women who do not need future fertility. The procedure includes removal of the descended vaginal compartment and closing of the vagina (the uterus may or may not be removed). Reconstructive surgery is aimed to maintain the normal pelvic anatomy. The procedure involves paravaginal repair and vaginal vault suspension by utero-sacral ligaments ([3](#_ENREF_3), [19](#_ENREF_19), [33](#_ENREF_33)). Currently, surgical management of POP is challenging as the need for uterine preservation is increased ([109](#_ENREF_109)). The procedure can be performed vaginally or abdominally ([3](#_ENREF_3), [19](#_ENREF_19), [33](#_ENREF_33)).

While it is the commonly used treatment technique in low-income countries, still it has both anatomical and symptomatic recurrence. Intraoperative damage to connective tissues, blood supply, and nerves was found to increase central compartment prolapse ([4](#_ENREF_4)). A follow-up study of women who underwent surgery from 2015-17 in Mekele, Ethiopia, showed that vaginal repair has an anatomical failure in 34% and symptomatic recurrence in 23% ([33](#_ENREF_33)).

## Justification of the Proposed Study

In addition to the universally identified risk factors, there are additional risk factors in Ethiopia that are expected to increase the prevalence of POP. Women in Ethiopia are prone to a high number of vaginal deliveries, early marriage, early childbirth, heavy lifting/carrying, and low body mass index ([38-40](#_ENREF_38)).

Studies conducted in Ethiopia on the POP prevalence and risk factors were systematically searched in PubMed using key terms and 23 studies were identified. Google Scholar, African Journal of Online, and Directory of Open Access Journals were also searched for important literature. Most of the identified studies were health facility-based ([27](#_ENREF_27), [35](#_ENREF_35), [36](#_ENREF_36), [40](#_ENREF_40)); and the other studies were conducted using the symptomatic approach for POP diagnosis ([41](#_ENREF_41)). Both approaches have a high probability of underestimating the prevalence of POP. It is evidenced that pain and severe difficulties while carrying out daily activities were common with POP patients. However, patients do not disclose it and seek treatment since the disclosure was related to discrimination, stigma, and divorce ([27](#_ENREF_27)). Almost 80% of POP patients from Pakistan and Ethiopia were delayed at least for 12 months before seeking treatment for severe degree prolapse ([26](#_ENREF_26), [35](#_ENREF_35), [36](#_ENREF_36)). Therefore, a community-based study is important to reveal the prevalence in at early stage in the general population. Unlike the previous studies, the risk factors will be identified by using a complex survey analysis that matches with sampling design.

Moreover, since there is a lack of evidence about the effect of PFMT in prolapse symptom management in low-income countries like Ethiopia, this study will evaluate its effect both on prolapse symptom and quality of life.

## Significance of the Study

Understanding about the epidemiology of POP has both clinical and public health importance. In general, POP has significant public health importance as it decreases the quality of life, increase the use of health care resource and decrease productivity ([37](#_ENREF_37)). It is an important public health issue that needs to be a focus of primary prevention ([110](#_ENREF_110)). As a result of lifestyle modification, it is expected that the number of elderly population will increase from time to time, and the POP will become more prevalent shortly and increase economic and public health burden ([2](#_ENREF_2), [4](#_ENREF_4), [15](#_ENREF_15)). The increase in life expectancy and improved quality of life increase both the prevalence of disease and the number of treatment-seeking women ([4](#_ENREF_4)). As a public health concern, at least to allocate resources to women with POP, an understanding of its incidence/prevalence, risk factors, clinical implication, and treatment options are needed to treat and develop preventive strategies. Identifying modifiable risk factors may also help for patient counselling and prevention in patients at risk ([2](#_ENREF_2)). Since the risk factors of POP are multifactorial, the approach to risk factor modification and prevention may also differ across settings ([63](#_ENREF_63)). So, to develop the best and most- effective preventive and therapeutic strategies, the prevalence and risk factors at the community level should be defined ([37](#_ENREF_37)). Therefore, this study will determine the prevalence and identify associated risk factors of POP among women in Sidama National regional State. The regional health bureau and other organizations working on women's health will use the findings.

On the Clinical aspect, as its current status, the high cost for treatment and risk of recurrence after surgery makes POP both a health and financial burden ([2](#_ENREF_2)). POP is currently a common disorder that has a remarkable economic burden on the health system and individuals ([7](#_ENREF_7)). Health care providers need to understand epidemiology to screen for the disorders and treat them to improve quality of life and decrease the economic burden of individuals and the health care system ([111](#_ENREF_111)).

The demand for conservative management is common especially for women giving birth at an older age ([109](#_ENREF_109)). Moreover, currently, the most important outcome of POP treatment is health-related quality of life and patient satisfaction ([14](#_ENREF_14), [112](#_ENREF_112)). POP causes a vaginal bulge, voiding dysfunction, and sexual dysfunction which adversely affects the quality of life ([9](#_ENREF_9), [14](#_ENREF_14)). Sexual function is complex and may not be managed with surgery for POP. The relationship status and sexual desire might not improve by structural change (surgery) ([31](#_ENREF_31)).

If the result of the current study is effective in improving prolapse symptoms and quality of life, the intervention will be expanded to wider areas. Therefore, evaluating the effectiveness of this non-surgical, cheap and no side effect treatment option has important value to improve women's health. This study will also reveal how much women’s health-related quality of life is affected by prolapse symptoms. This in turn will contribute to enabling the family and community to understand and help women with pelvic organ prolapse. The long-term goal of this study is to produce knowledge used to improve health care for women with Pelvic Organ Prolapse in Sidama National Regional State, Ethiopia.

# **OBJECTIVES**

# **3.1** General Objective

To Assess the Prevalence and risk factors of Pelvic Organ Prolapse; and Effect of Pelvic Floor Muscle Training on Prolapse Symptom and Quality of Life in Sidama National Regional State, Ethiopia, 2022.

# **3.2.** Specific Objectives

1. To Translate the Pelvic Organ Prolapse Symptom Score (POP-SS) into Sidaamu Afoo and Evaluate its Psychometric Properties.
2. To determine the prevalence and identify the risk factors of pelvic organ prolapse in Sidama National Regional State
3. To evaluate the effect of Pelvic Floor Muscle Training for reducing pelvic organ prolapse symptoms among women with POP in Sidama National Regional State
4. To evaluate the effect of Pelvic Floor Muscle Training to improve Prolapse Quality of Life among women with POP in Sidama National Regional State.

# **METHODS**

This study will be conducted in two phases. Phase one is used to address objective one and two, and the second phase will be conducted to answer objectives three and four.

# **PHASE-I PROJECT**

# **PAPER-I**

Validation of the Sidaamu Afoo version of the Pelvic Organ Prolapse Symptom Score in Sidama National Regional State, Ethiopia, 2022.

## Objective

To Translate the Pelvic Organ Prolapse Symptom Score into Sidaamu Afoo and evaluate its psychometric properties among Sidaamu Afoo speaking women, in Ethiopia, 2022.

## The Original POP-SS questionnaire

The original version of the POP-SS was initially developed by [name] in English Speaking women ([16](#_ENREF_16)). Later it was translated to and validated in Turkish, Amharic, and Chinese ([113-115](#_ENREF_113)). The POP-SS has seven questions with a five-point Likert scale which ranges from zero to four (0= never felt symptom, 1= occasionally, 2= sometimes, 3= most of the time, and 4= all of the time), a higher score indicating severe symptoms ([16](#_ENREF_16)). The participants will be asked how often they have had the following symptoms in the last four weeks: 1) A feeling of something coming down from the vagina? 2) Uncomfortable feeling in the vagina that worsens when standing? 3) A heaviness feeling in the lower abdomen? 4) A dragging feeling in the lower back? 5) A difficulty of emptying the bladder? 6) A feeling of incomplete bladder emptying? 7) A feeling of incomplete bowel emptying? The total score will be calculated by summing up all responses for the seven-question and the total score will range from 0 to 28. If the participants' total response score is different from zero, she will be considered as having symptoms of prolapse.

To increase the accuracy of measurements, instrument (data collection tool) translation, cross-cultural adaptation, and validation for the language of the target population are mandatory ([116-118](#_ENREF_116)). Therefore, this study is aimed to translate and validate the POP-SS tool in Sidamu Afoo.

## Translation and Cultural Adaptation of POP-SS

Translation and cultural adaptation of the POP-SS tool will be conducted according to the standard method of translation and adaptation recommendation ([117](#_ENREF_117)). The permission to translate the tool will be received from the original author of the POP-SS, [name] ([16](#_ENREF_16)).

**Forward Translation**: Three native Sidaamu Afoo speakers (two gynecologists and one sociologist) who are fluent in English will translate the tool from English to Sidaamu Afoo independently. A common draft version of Sidamu Afoo will be produced from the three translated versions in consensus between the three authors and one language expert. This version will be back-translated into English by two independent fluent English and Sidaamu Afoo speakers. The original and back-translated versions will be checked for any discrepancies by the authors and referred back to the developers for conceptual equivalence. After incorporating necessary changes or comments, the first Sidaamu Afoo version will be produced.

For expert committee review, expertise from gynecology, midwifery, public health, and Sidaamu Afoo instructors will review the final forward and backward translations against the original version. All issues, if present, will be addressed and a preliminary version will be created and circulated among review members. The expert committees will evaluate the suitability of each item and rate its relevance. The agreement will be calculated using the Content Validity Index ([119](#_ENREF_119)).

To evaluate the equivalence and comprehensibility of the translated Sidaamu Afoo version, it will be face-validated and pretested among ten women who speak Sidaamu Afoo and admitted to Adare General Hospital and Yirgalem Hamlin Fistula Center with a diagnosis of POP.

## Study Participants

The study participants will be women aged 18 years and above who visit the gynecology outpatient department (clinics) of Adare General Hospital and Yirgalem Hamlin Fistula Center from April 01 – to May 30, 2022 will be recruited consecutively.

## Sample Size

To ensure the statistical robustness of the analysis, the sample size is determined based on the recommendation of at least 5-10 subjects per item of the tool by the consensus-based Standards for the Selection of the Health Measurement Instruments (COSMIN) ([120](#_ENREF_120), [121](#_ENREF_121)). Accordingly, the estimated sample size is 70 (10 subjects per item).

## Sampling Procedure

All women who visit gynecology outpatient departments of Yirgalem Hamlin Fistula Center and Adare General Hospitals during the study period will be assessed for the presence of prolapse symptoms by two important questions. Women will be asked whether they had a feeling of bulging/pressure/something coming down from their vagina or whether they had a visible mass protruding from the vagina in the past one year ([114](#_ENREF_114), [122](#_ENREF_122), [123](#_ENREF_123)). All women who have the above symptom will be invited for pelvic examination to confirm the prolapse. To measure the test-retest reliability, 35 women who will complete the questionnaire two weeks later will be purposefully selected based on their accessibility after two weeks. Then all women will be examined and the stage of prolapse will be classified according to the standard Pelvic Organ Prolapse Quantification system.

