Test-retest reliability will be computed based on the Intra-class Correlation Coefficient (ICC). Single rating, absolute agreement, and a two-way mixed-effect model will be used and an Intra-class Correlation Coefficients (ICC) of ≥ 0.7 will be accepted ([120](#_ENREF_120)).

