## Study Setting and Period

This study will be conducted in the Dale and Wonsho districts of Sidama National Regional State, Ethiopia from 01 June – 24 July 2022. Both woredas are known for their highly dense population and coffee production. Dale district (woreda) has 10 health centers and 33 health posts. Hamlin Fistula Center, which provides care for fistula cases and pelvic organ prolapse is found in Yirga-Alem town in Dale district. Wonsho district has five health centers and 17 health posts. According to the 2021 report of Sidama Regional Health Bureau, the total population of Dale district is 254,653 and that of Wonsho district is 129,730 ([134](#_ENREF_134)). According to the Ethiopian Central Statistical Agency, the female population accounts for 49.7% of Dale woreda population and 49.2% of Wonsho population ([135](#_ENREF_135)). Dale district has 36 rural and two urban kebeles while Wonsho district has 17 rural and one urban kebeles (smallest administrative units in Ethiopia).

In 2017, Hawassa University has established its own Health and Demographic Surveillance System site in Dale and Wonsho districts of Sidama Region. The HDSS site include 10 rural kebeles and two urban kebeles. The Surveillance site is called Dale-Wonsho Health and Demographic Surveillance Site (D-W HDSS). The Map of the HDSS site is obtained from previous study (Figure 2).

[figure not shown]

Figure 2: Map of Hawassa University Health and Demographic Surveillance System Sites from Dale and Wonsho Districts ([136](#_ENREF_136)).

.

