## Data Collection Tools and Procedure

The Pelvic Organ Prolapse symptoms will be assessed using a translated and validated Sidaamu Afoo version of the POP-SS questionnaire. This tool will be obtained from Paper I of this dissertation project (Paper I). After the intervention, in addition to the POP-SS tool, the Patient Global Impression of Change (PGIC) tool will be used to evaluate patients’ perceived change in prolapse symptoms. The PGIC evaluates overall health status as perceived by the patient in a seven-point single item scale measured as 1= very much improved, 2= much improved, 3= minimally improved, 4 = no change, 5= minimally worse, 6= much worse or 7= very much worse. This scale can be classified into three major categories for description purposes: worsen or disease deterioration (very much worse, much worse, or minimally worse), the same (no change), and improved (minimally improved, much improved, and very much improved) (27). The PGIC will be translated into Sidaamu Afoo by native speakers and translated back to English to check its consistency.

After six months of intervention, the same data collectors of the baseline data will go to the house of the study participants and collect the data through face-to-face interviews. These data collectors are those who were recruited by Hawassa University to collect data from the HDSS site and fluent in Sidaamu Afoo.

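### The two-week POP-SS retest has no stability anchor, so real symptom change counts as measurement error and the ICC can understate reliability

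*Protocol*

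**What the plan says.** Paper-I recruits women consecutively from the gynaecology outpatient services of Adare General Hospital and Yirgalem Hamlin Fistula Center. It screens them for prolapse symptoms and confirms prolapse by pelvic examination. For reliability over time, Sampling Procedure says that "35 women who will complete the questionnaire two weeks later will be purposefully selected based on their accessibility after two weeks". Statistical Analysis fixes the estimator and the rule: "Single rating, absolute agreement, and a two-way mixed-effect model will be used and an Intra-class Correlation Coefficients (ICC) of ≥ 0.7 will be accepted".

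Three other places bear on the point:

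- **Care at the recruiting site.** Paper II, Study Setting and Period, describes the "Hamlin Fistula Center, which provides care for fistula cases and pelvic organ prolapse". In Paper-I, the pretest under Translation and Cultural Adaptation draws on women admitted to both sites with a prolapse diagnosis.
- **Recall period.** The POP-SS asks "how often they have had the following symptoms in the last four weeks".
- **Global-change questions.** Paper-III, Data Collection Tools and Procedure, says "The PGIC will be translated into Sidaamu Afoo by native speakers". Annex II restricts this item, and its counterpart in the quality-of-life part, to the six-month end-line.

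The Paper-I sections set no requirement that retested women be unchanged, ask no change question at the second interview, and record no care received between the two interviews.

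**The concern.** A test-retest ICC isolates measurement error only in people whose true state is the same on both occasions. Where some women really improve or worsen, their change enters the ICC as disagreement. The absolute-agreement form also penalises a shift in the mean, which is what improvement after care would produce.

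The Sidaamu Afoo POP-SS is the trial's primary outcome measure and supplies its symptom entry criterion. If the ICC came out low, the investigators could not tell a weak translation from real change in some of the women. An analysis plan written later could not separate the two either, because the data would never have been collected.

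**Working it through.** **Inputs from the protocol.** 35 retested women; ICC criterion 0.7; seven items scored 0 to 4, total 0 to 28; four-week recall; two-week interval. The only POP-SS changes given are those in the Paper-III sample size section, over six months: mean 3.16 (SD 4.78) with pelvic floor muscle training and 0.12 (SD 3.86) in controls.

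**The plan's own figure.** 10 subjects × 7 items = 70, which reproduces the validation sample. The retest number of 35 is half of that. No calculation is given for 35.

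**Assumptions not in the protocol.** Score SD S = 6 and mean 12; true ICC in stable women R = 0.80, 0.85 or 0.90; a fraction f of women falls by D points between interviews, independently of baseline. The value D = 3.16 borrows the protocol's six-month mean as a yardstick. D = 6 is a deliberately large change.

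**Population ICC.** The between-women variance is R·S². Real change adds f(1−f)D² to the second-occasion variance and shifts the mean by fD. Averaging the two variances and adding half the squared mean shift gives

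ICC = R·S² / (S² + f·D²/2).

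For S = 6, R = 0.80 and f = 0.20:

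- all stable: 28.8 / 36 = 0.80
- D = 3.16: 28.8 / (36 + 0.2 × 9.99 / 2) = 28.8 / 37.0 = 0.78
- D = 6: 28.8 / (36 + 0.2 × 36 / 2) = 28.8 / 39.6 = 0.73

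**Chance that the estimated ICC reaches 0.7.** Simulation with n = 35, scores rounded and limited to 0–28, 20,000 samples per setting:

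| True ICC | All stable | 20% fall by 3.16 | 20% fall by 6 |
|---|---|---|---|
| 0.80 | 90% | 83–84% | 62% |
| 0.85 | 99% | 96% | 81–82% |
| 0.90 | nearly 100% | nearly 100% | 95% |

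**Sensitivity.** A second run without rounding or limits took S from 4 to 6, R from 0.80 to 0.90 and f = 25%. The chance of missing 0.7 ran from 0.3% to 30% when the change was 3.16 points, and from 9% to 79% when it was 6 points.

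**With an anchor.** If the 20% who changed were identified without error, 35 × 0.8 = 28 women would remain. At a true ICC of 0.80 the chance of reaching 0.7 would then be about 88%.

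**The case against.** The strongest reply is that large real change within two weeks is unlikely. The protocol's own mean change with training is 3.16 points over six months, and in controls it is close to zero. Statement of the Problem says pessary and pelvic floor training are not yet in use in Ethiopia apart from a pessary pilot, and the literature review says women in developing countries are usually managed surgically. Nothing suggests that a tenth or a fifth of outpatients would be operated on between interviews. With a four-week recall, about half of the second window repeats the first, which damps recent change, and memory of earlier answers pushes the ICC up. All of this stands. It makes the likely loss modest, though the six-month SDs of change (3.86 and 4.78) show that individuals can move by more than the mean.

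Three stronger readings are tempting, and the protocol does not support them.

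- **That choosing women by accessibility causes the problem.** It does not create symptom change, and consecutive selection would not remove it. Choosing women who can be reached is a practical way to complete a retest.
- **That this rule alone decides whether the POP-SS is accepted.** Content validity, Cronbach alpha, item-total correlation, factor structure and known-group comparison are also assessed. No consequence is stated for an ICC below 0.7.
- **That a sound instrument will probably fail.** At a true ICC of 0.85 or above, a likely failure needs many women changing by a large amount.

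Nor does the gap bias the trial's comparison between arms. Its effect is on the reliability reported in Paper-I.

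**Conclusion.** The point holds as a gap in design: the retest cannot distinguish unreliability from real change, and what is missing must be collected at the second interview. The direct effect of unrecorded change is to understate reliability. At a true ICC of 0.80 and SD 6, the cost in pass probability is about 6 percentage points if 20% of women change by 3.16 points, and about 28 if 20% change by 6 points. At 0.85 to 0.90 it is smaller. These figures rest on the assumed SD, true reliability, share changing and size of change. They do not model recall overlap or memory. The conclusion is that the ICC can fall short of 0.7 for this reason, not that it will. This is a modest weakness that is inexpensive to repair.

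**What to change.** At the second interview add two questions:

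1. A single global-change item. The PGIC is already due for translation, but its end-line wording refers to the start of the intervention, so it must be reworded to ask about change since the first interview.
2. A yes/no item on whether any prolapse care has begun since the first interview.

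Apply the 0.7 criterion to women who report no change and no new care. Report the ICC in all retested women beside it, with both sample sizes.

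The cost is two short questions, one rewording, and somewhat fewer than 35 women in the ICC that is judged. A single recall item will also misclassify some women, so the anchor reduces the problem without removing it. No change to selection or to clinical care is needed.
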